# Prospective, non-randomised, open-label pilot trial assessing feasibility, safety and treatment success of acupuncture in children with functional constipation: ACU-PILOT study protocol

**DOI:** 10.1136/bmjopen-2025-109425

**Published:** 2025-11-11

**Keywords:** Motility disorders, Acupuncture, Functional bowel disorders, Paediatric gastroenterology, Child

## Abstract

**Introduction:**

Functional constipation (FC) is prevalent among children and often persists despite standard pharmacological treatment with oral laxatives. Many parents turn to complementary therapies, including acupuncture, which has been shown to relieve symptoms in adults with FC. However, studies in children with FC are scarce and have important limitations. This study will evaluate the feasibility, safety and potential efficacy of acupuncture for children with FC.

**Methods and analysis:**

Prospective, non-randomised, open-label pilot study in children with FC (6–18 years). Participants will undergo eight acupuncture sessions over 10 weeks. Concurrent pharmacological treatment with polyethylene glycol (≥0.2 g/kg/day) will continue as initiated prior to enrolment. The primary endpoint is feasibility, defined by an attrition rate of ≥70%. Secondary feasibility endpoints include consent rate, patient/parent satisfaction and personnel requirements. Safety will be assessed by systematic monitoring of adverse events. Efficacy endpoints include treatment success, defined as no longer meeting the Rome IV criteria for FC at the end of the intervention period, as well as defecation frequency, stool consistency, painful defecation, faecal incontinence frequency, abdominal pain, medication use and quality of life, based on a previously published core outcome set.

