### Outcomes

#### Primary outcome

##### Feasibility

Attrition rate, defined as the percentage of participants completing the study protocol. The intervention will be considered feasible if ≥70% of participants complete the study while attending ≥75% of acupuncture sessions.

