### Statistical analysis

Continuous data will be presented as mean±SD if normally distributed and as median with IQR otherwise. Categorical data will be presented as proportions. The 95% CI will be calculated for all primary and secondary parameters, with significance set at α=0.05. The primary outcome, attrition rate, is defined as the proportion of participants completing the study. Attendance at 100%, ≥75% and ≥50% of acupuncture sessions will be reported. Feasibility is confirmed if ≥70% of participants complete the study while attending ≥75% of sessions, informing a future RCT design. Secondary feasibility outcomes include consent rate, satisfaction and personnel capacity. Consent rate is the proportion of approached participants who provided consent, with age distribution reported as mean±SD or median (IQR). Reasons for non-participation will be described. Satisfaction scores (5-point Likert scale) at weeks 6, 10 and 14 will be summarised, visualised with bar plots and analysed descriptively. Personnel requirements will be summarised.

A table will summarise acupuncture points. Safety analysis includes AE frequency. Efficacy, assessed as the proportion no longer meeting Rome IV criteria, will be analysed using McNemar’s test. Due to the study design, no efficacy claims can be made without a control group.

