### Interim analysis

An interim analysis will be conducted after 10 participants have completed the study, including follow-up, to evaluate feasibility. This unblinded analysis will assess attrition rate, consent rate, patient and parent satisfaction, and retention rate. The interim findings will be discussed with the research team to determine whether the study should continue as planned. The principal investigator will make the final decision regarding trial continuation and will report this decision to the METC.

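### The primary endpoint is mislabelled as attrition, and its definition omits the attendance condition in its own decision rule

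*Protocol article*

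**What the plan says.** The primary endpoint appears in four places in the protocol article.

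- Abstract, Methods and analysis: "The primary endpoint is feasibility, defined by an attrition rate of ≥70" per cent.
- Outcomes, Primary outcome: "Attrition rate, defined as the percentage of participants completing the study protocol". The decision rule follows: "The intervention will be considered feasible if ≥70% of participants complete the study while attending ≥75% of acupuncture sessions".
- Statistical analysis: "The primary outcome, attrition rate, is defined as the proportion of participants completing the study". The rule is then repeated: "Feasibility is confirmed if ≥70% of participants complete the study while attending ≥75% of sessions".
- Interim analysis: "This unblinded analysis will assess attrition rate, consent rate, patient and parent satisfaction, and retention rate".

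Two further sentences in Statistical analysis bear on what will be reported. On precision: "The 95% CI will be calculated for all primary and secondary parameters, with significance set at α=0.05". On attendance: "Attendance at 100%, ≥75% and ≥50% of acupuncture sessions will be reported".

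**The concern.** There are two separate defects.

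The first is the label. Attrition means loss. The Abstract sets a floor of 70% on it, which reverses the criterion, and it gives no definition that would let its reader correct this. The body applies the same word to completion. The interim section then names both attrition and retention. If attrition means completion, as the body says, retention looks like the same quantity listed again. If it means loss, the interim contradicts the definition of the primary outcome.

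The second is the numerator. In Statistical analysis the primary outcome is completion alone, while the rule counts children who complete and also reach the attendance level. The primary parameter, to which the confidence interval is attached, is then not the quantity that settles feasibility.

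What is at stake is the number on which the decision to proceed to a randomised trial rests. A report could lead with a completion rate above 70% and its interval while the rule is failed on a smaller proportion that has no interval of its own.

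**Working it through.** **Inputs.** N = 18; expected feasibility 0.9, lower bound 0.7, alpha 0.05, power 0.8 (Sample size calculation). Eight sessions (Abstract). The 70% and 75% thresholds (Outcomes; Statistical analysis). Intervals below are exact (Clopper-Pearson) 95% intervals.

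**1. The plan's own figure.** The stated 18 is reproduced by n = (z0.975 + z0.80)² × 0.9 × 0.1 / (0.9 − 0.7)² = 2.8016² × 0.09 / 0.04 = 17.66, rounded up to 18. An expected value of 0.9 above a lower bound of 0.7 makes sense only for a success proportion, so the sample size section agrees in direction with the body.

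**2. Thresholds as counts.** 0.70 × 18 = 12.6, so at least 13 children are needed. 0.75 × 8 = 6 sessions.

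**3. The Abstract taken literally.** Attrition of at least 70% means at least 13 of 18 drop out, so at most 5/18 = 27.8% complete. With a true completion rate of 0.9, the probability of 13 or more drop-outs is about 5 × 10⁻¹⁰. This cannot be what is meant.

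**4. The numerators side by side.**
- Outcomes, definition: finishing the study protocol (attendance possibly implied).
- Statistical analysis, definition: finishing the study (no attendance condition).
- Rule, both sections: finishing the study and attending at least 6 of 8 sessions.

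**5. How far the two rates can differ (illustrative counts).**
- Completion alone: 14/18 = 77.8% (52.4% to 93.6%).
- Two of those 14 attended fewer than six sessions: 12/18 = 66.7% (41.0% to 86.7%), not feasible.
- The smallest passing result on the joint quantity: 13/18 = 72.2% (46.5% to 90.3%).

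**6. Does the separate attendance table close the gap?** Not fully. If 14 complete and 14 attend at least six sessions, the number doing both lies between 14 + 14 − 18 = 10 and 14, that is 55.6% to 77.8%. That range spans the 70% threshold. The two marginal figures bound the joint proportion but do not fix it.

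**7. Range over an unknown.** The article gives no expected attendance. Assume true completion of 0.9 and let q be the probability that a completer attends at least six sessions. The joint rate is 0.9q:

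| q | joint rate | P(at least 13 of 18) |
|---|---|---|
| 1.00 | 0.900 | 0.994 |
| 0.95 | 0.855 | 0.964 |
| 0.90 | 0.810 | 0.890 |
| 0.85 | 0.765 | 0.767 |
| 0.80 | 0.720 | 0.609 |

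Completion alone would reach 13 of 18 with probability 0.994 whatever q is.

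**8. Denominator.** The section on premature termination replaces children who withdraw during run-in or for reasons unrelated to the study. Whether a replaced child stays in the denominator can matter: 13/18 = 72.2% passes, while 13/19 = 68.4% does not.

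**The case against.** The strongest reply is that nobody running the trial from the body text would go wrong. The joint rule is given twice in the same terms and in the right direction, and the sample size section agrees with it. This stands, and it limits the point. A reader might infer from the Abstract that the trial could be declared feasible on mass drop-out; the documents do not support that.

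A reader might also infer that the plan yields two conflicting verdicts. It does not. Feasibility is tied only to the joint rule, so the 12/18 example is not feasible however many children complete. The conflict is between the headline estimate and the deciding quantity.

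Third, it is tempting to say that a child who attends a few sessions and returns for the last visit counts as a primary-outcome completer. Under the Outcomes definition this is not secured, because completing the study protocol may already include attendance. It is firmer under Statistical analysis, where the definition has no attendance condition and the rule adds one.

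Fourth, the promise of intervals for all primary and secondary parameters does not exclude one for the joint proportion, and a fuller document might provide it. That is fair. But the article itself says what the primary outcome is, and as defined there it is completion.

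Finally, the interim sets no numerical threshold on attrition or retention, so no threshold is inverted there. Only the terms are unclear.

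**Conclusion.** The point holds as a defect of labelling and definition. The Abstract's criterion is wrong as written, the word attrition is used for its opposite in the body, and the primary outcome in Statistical analysis lacks the attendance condition on which its own rule depends. The go/no-go rule is recoverable and its thresholds are not in dispute.

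The practical size depends on how many completers attend fewer than six sessions, which the article does not let us estimate. If none do, the two rates coincide. With two such children among 14 completers, the headline is 77.8% and the deciding rate 66.7%. The probabilities in the table rest on an assumed completion rate of 0.9 and on the assumed range for q.

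**What to change.** - Replace attrition rate with completion rate throughout, and correct the Abstract to the body's rule: feasible if at least 70% of participants both finish the study and attend at least 75% of sessions (6 of 8).
- Make that joint proportion the single primary parameter in Outcomes and Statistical analysis, reported with its 95% CI. Give completion alone and the attendance levels as components.
- State the denominator in the same place, and say how replaced participants are counted under the replacement rule.
- At the interim, use the same single term in place of the attrition and retention pair.

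The cost is wording in the Abstract, Outcomes, Statistical analysis and Interim analysis sections, and in the registry entry if it repeats the phrase. The denominator is the one item that needs a decision, best made before the interim look. N = 18 and the 70% and 75% thresholds stay as they are, taking the planning value of 0.9 to refer to the joint proportion, which the article should confirm.

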**Ethics and dissemination:**

Ethical approval was provided by the Medical Ethics Committee of Amsterdam UMC (Netherlands; NL87083.018.24). Results will be published in peer-reviewed journals and presented to scientific and consumer audiences.

**Trial registration numbers:**

NCT06836362 and NL-OMON57236.

STRENGTHS AND LIMITATIONS OF THIS STUDYThe open-label design and continuation of standard pharmacological treatment enhance the applicability of findings to current clinical practices worldwide.Strict inclusion criteria requiring polyethylene glycol as primary pharmacotherapy and allowing limited stable co-medication ensure greater uniformity within the study group but may limit the generalisability of results to children receiving other treatments for functional constipation, such as other medications or trans-anal irrigation.Acupuncture is administered according to a semi-standardised protocol, combining a core set of acupoints with individualised point selection based on clinical assessment.Feasibility endpoints, including attrition rates and satisfaction, will inform the potential design of a future randomised controlled trial.While efficacy will be measured, the absence of a control group limits the assessment of acupuncture’s clinical efficacy.

## Introduction

 Functional constipation (FC) is a common disorder in children and adolescents with a worldwide pooled prevalence of 9.5%.^1^ It is characterised by infrequent, painful, hard stools and is often accompanied by faecal incontinence and abdominal pain.^2^ FC is a clinical diagnosis based on history and physical examination and is defined according to the Rome IV criteria (table 1).^3^ It has a significant psychological impact on the quality of life of children and their parents.^4 5^ In addition, FC, often accompanied by symptoms of faecal incontinence, can negatively affect the healthy psychosocial development of children and lead to feelings of frustration among parents.^6^

**Table 1 T1:** Eligibility criteria for participants

Inclusion criteria	Exclusion criteria
6–18 years of age	Irritable bowel syndrome (IBS)*
Insufficient symptom management† despite ≥3 months of medical management (including education, non-pharmacological advice and laxatives) by a physician	Organic causes of constipation (eg, spina bifida or Hirschsprung disease)
Are treated with PEG (minimum dose of 0.2 g/kg/day) for ≥1 month prior to inclusion in the study	Concomitant use of drugs not intended for FC treatment that are known to affect gastrointestinal motility
Meet the modified Rome IV criteria for children and adolescents with FC^3^‡:	Previously received acupuncture for constipation or currently participating in another clinical trial
1) ≤2 spontaneous bowel movements (SBMs) per week (SBM *defined as* a bowel movement that occurs in the absence of laxative, enema or suppository use in the preceding 24 hours)	Significant chronic health conditions requiring specialty care (eg, cardiac, renal or metabolic diseases) that could impact the child’s ability to participate or confound the results of the study
2) History of excessive stool retention	Recurrent or unexplained fevers
3) History of painful or hard bowel movements	Pregnancy
4) History of large-diameter stools	Smoking
5) Presence of a large faecal mass in the rectum	Severe needle-related anxiety
6) ≥1 episode/week of incontinence after the acquisition of toileting skills	History of abdominal surgery except appendectomy or hernia repairs
7) History of large-diameter stools that may obstruct the toilet in toilet-trained children	Unintentional weight loss ≥5% of body weight within the last 3 months
Written informed consent (parents/guardians and children ≥12 years)	Clotting disorders or recent history of thrombocytopenia
	Immunocompromised children
	Established diagnoses of autism spectrum disorders
	Established major psychiatric disorders or a history of abuse
	Rash or active local infection over an acupuncture point

* Rome IV criteria (fulfilled for ≥2 months before diagnosis) for IBS in children and adolescents include all of the following: (1) Abdominal pain at least 4 days per month associated with one or more of the following: (a) Related to defecation. (b) A change in frequency of stool. (c) A change in the form (appearance) of stool. (2) In children with constipation, the pain does not resolve with resolution of the constipation (children in whom the pain resolves have functional constipation, not IBS). (3) After appropriate evaluation, the symptoms cannot be fully explained by another medical condition.

† Insufficient symptom management is defined as the presence of ≥1 of the Rome IV criteria for FC *despite* medical management by a physician.

‡ Defined as meeting ≥2 of the following criteria during the 2-week run-in period despite receiving treatment with PEG (min. 0.2 g/kg/day).

FC, functional constipation; PEG, polyethylene glycol.

From a global health perspective, the burden of FC on healthcare and healthcare costs is significant. Due to the protracted nature of childhood FC, it accounts for up to 25% of visits to paediatric gastroenterologists in the USA.^7^ Annual healthcare costs related to FC vary between studies but are estimated to be three times higher in children with FC than for children without constipation, accounting for an additional cost of up to $3.9 billion/year in the USA alone.^8 9^

Initial treatment consists of non-pharmacological and pharmacological interventions.^10^ Non-pharmacological interventions involve education and demystification, toilet training (with a reward system), and keeping a defecation diary. First-line pharmacological treatment involves oral osmotic laxatives, preferably polyethylene glycol (PEG).^10^ Osmotic laxatives are considered safe, but adherence to PEG is generally low.^11^ In rare cases, surgical interventions such as antegrade continence enemas or colonic resections with or without diverting ostomy are performed as a last resort.^12^

Despite these different interventions, approximately 40% of children with FC referred to a paediatric gastroenterologist remain symptomatic after 5 years, and even after 10 years of treatment, 20% of children still suffer from FC symptoms.^10^ Unresolved, chronic symptoms may lead to a search for alternative treatment strategies. A Dutch study in 2008 reported that almost 40% of parents of paediatric patients with functional and organic gastrointestinal diseases use complementary and integrative medicine for their child.^13^ However, evidence to support such practices in children is often lacking or of low quality. Therefore, there is an urgent need for high-quality research in this field to uncover both potential benefits and possible risks related to practices that have not yet been studied adequately but are currently being performed on children worldwide.

Acupuncture is an ancient therapeutic technique that involves stimulating specific acupuncture points on the body, known as acupoints, aiming to modulate physiological responses. Stimulation of acupoints can occur through several mechanisms, including non-invasive paediatric techniques such as Shonishin, which involves gentle tapping, rubbing or pressing of the skin to stimulate acupoints, laser techniques (laser acupuncture) or the insertion of fine needles (manual acupuncture) potentially accompanied by electrical stimulation (electro-acupuncture).^14 15^ In China, acupuncture has been used for thousands of years and in recent times a considerable number of studies have been performed on acupuncture for the treatment of disorders of gut-brain interaction in adults, including FC.^16 17^ Results of several randomised controlled trials (RCTs) in adults indicate that acupuncture may be effective in treating FC by increasing stool frequency, improving stool consistency, alleviating constipation symptoms and improving quality of life.^16^ However, these studies have used a variety of study designs, are often of poor quality and have mostly been performed in China.^16^

Although the exact mechanisms of acupuncture are not fully elucidated, acupuncture is thought to potentially improve FC symptoms via multiple mechanisms, including regulation of both the enteric nervous system and the central nervous system, thereby improving gut motility.^16^,^18^ The regulatory system linking the central and enteric nervous system to the peripheral intestinal functions is referred to as the brain-gut axis. This complex bidirectional system includes the parasympathetic and sympathetic nervous system, endocrine and immune factors, and the gut microbiota, all regulating gastrointestinal homeostasis.^19^,^21^ The vagal nervous system, as main component of the parasympathetic nervous system, is important in the regulation of the gastrointestinal system,^21^ exerting both excitatory and inhibitory control over the gastrointestinal tract.^18^ The role of the sympathetic nervous system is mainly inhibitory^18^ and it is likely that its activation via release of stress hormones such as epinephrine, norepinephrine and cortisol contributes to a dysregulation of gut motility.^22^ Some studies in animals and humans have suggested a role for acupuncture via regulation of the enteric nervous system, although mostly in the context of visceral pain management.^23^,^29^

Although several researchers have attempted to elucidate possible mechanisms of action of acupuncture, it is challenging to pinpoint a single mechanism. This may partially be due to the diversity of acupuncture techniques, variations in local receptor types and densities at different points (including neuroreceptors, mechanoreceptors or receptors on immune and interstitial cells) and differences in which receptors are activated depending on the depth and method of needling.^28^,^31^ Any potential effects of acupuncture are most likely explained by a combination of various factors.

To date, although promising, published data on the effects of acupuncture on FC symptoms in children are limited^32^,^34^ and published reports in adults have important limitations to take into consideration when interpreting these results.^16^ Anders *et al* applied a single acupuncture treatment with fixed indwelling acupuncture needles in 10 children (0.5–15 years) with hospital-induced constipation (defined as no stool within 72 hours after hospital admission) before conventional therapy with laxative suppositories was initiated.^33^ Patients, parents and nurses were encouraged to perform needle stimulation at acupuncture point LI-11 by means of massage for 2–3 min two times an hour. After stimulation of acupuncture point LI-11, defecation occurred within 2 hours in all patients without the need for administration of conventional laxative treatment. Broide *et al* included 27 constipated children (aged 3–13 years old) administering five weekly sham acupuncture sessions, followed by ten weekly true acupuncture sessions on LI-2, LI-4 and/or ST-36.^32^ A significant effect was reported of true acupuncture sessions on defecation frequency compared with baseline. The authors hypothesised that the effect of acupuncture may have been related to the release of opioid peptides. In their study population, they found a low basal plasma panopioid activity in constipated children compared with a healthy control group, which slowly increased during the study period. Abd El Azeem *et al* included 40 constipated children (aged 5–15 years old) in an RCT, comparing standard non-pharmacological interventions in combination with either laser acupuncture or lactulose.^34^ Laser acupuncture was performed at ST-25, ST-36, ST-37, BL-25 and LI-11 three times weekly for 4 weeks. A significant increase in bowel movement frequency in both groups (four times and three times a week in the acupuncture vs the lactulose group, respectively) was reported, in favour of the laser acupuncture group, as compared with pretreatment frequency (two times a week in both groups). Notably, these effects persisted 3 months after discontinuation of treatment, suggesting acupuncture’s potential impact on FC.

In summary, the results of three studies performed in children with constipation have shown promising results.^32^,^34^ Clinical findings of randomised sham-controlled trials in adults also suggest a positive effect of acupuncture on FC symptoms.^16^ However, currently, there is not one uniform, well-established acupuncture treatment protocol for patients with FC, since trial designs in adults with FC have used varying protocols with different outcome measures.^16^ Moreover, although published data on the effectiveness of acupuncture for patients with FC are promising, there are important limitations to take into consideration when interpreting these results. First and foremost, the quality of currently published research is often poor.^16^ In recent guidelines on FC in adults, the European Society of Neurogastroenterology and Motility has recommended that better-designed trials are necessary before the utility of acupuncture in constipation can be evaluated.^35^ Another major limitation of the currently available evidence is that most of these data come from Chinese studies and publication bias may affect the validity and reliability of these data. Therefore, there is an urgent need to assess the applicability of acupuncture in Western care settings, with methods adhering to internationally accepted research standards. In addition, there is a general lack of studies with acupuncture in children with FC and it is uncertain if children respond similarly to adults with FC, since the pathophysiological mechanisms underlying FC may vary between children and adults.^12^

Thus, the primary objective of this pilot study is to assess the feasibility of acupuncture in children with FC using an intervention protocol which was based on the available literature and expert opinion.^1632^,^34 36^ We will test the integrity and feasibility of this intervention protocol; if deemed feasible, we will conduct an RCT using this intervention protocol. Secondary objectives are to assess safety, tolerability and potential clinical efficacy of acupuncture in children with FC. We intend to collect sufficient information on endpoints that are important to enable the design of a future RCT.

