### Medication and co-interventions

Participants will continue their prestudy PEG dosage (≥0.2 g/kg/day) and non-pharmacological constipation treatments as previously prescribed by the medical team in charge. Concomitant use of laxatives other than PEG and other than escape medication (such as other osmotic or stimulating laxatives, eg, magnesium hydroxide, sodium picosulfate) is permitted if participants have been treated for at least 3 months prior to study initiation, as it is considered unethical to require discontinuation of such established therapy. The use and dosage of these co-medications will be documented. Current medication unrelated to defecation (eg, asthma medication) should be maintained. Initiation of new FC treatments or PEG dose increases during the intervention is prohibited. PEG dose reductions, if prescribed, will be documented. New medical treatments during the study will be assessed for impact, with potential withdrawal if necessary. Any PEG dose increase after the final acupuncture session will be recorded during follow-up.

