#### Efficacy

Treatment success, defined as resolution of FC per Rome IV criteria at the end of the intervention (EOI).^3 37^ Rome IV criteria will be assessed by the investigator at the screening visit (visit 1) and at the EOI visit. For the EOI assessment, the criteria will be assessed over the last 4 weeks of the acupuncture intervention, or, in the event a participant discontinues the study prematurely within 4 weeks, over the intervention period. Other efficacy endpoints will be assessed via symptom diaries, the endpoints, including quality of life and school absence, are based on a previously published core outcome set^45^:

Defecation frequency (bowel movements/week).Stool consistency (Bristol Stool Scale).Painful defecation (yes/no).Faecal incontinence frequency (episodes/week).Withholding behaviour (yes/no).Abdominal pain (yes/no, Visual Analogue Scale score).Spontaneous bowel movements (>24 hours after escape medication).Time between acupuncture and defecation.Bowel movements <24 hours after acupuncture.Escape medication use and effect.

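### Table 1 counts a bowel movement as spontaneous only if no laxative was used in the prior 24 hours, which conflicts with required daily PEG and with the Efficacy section's definition

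*Protocol article*

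**What the plan says.** Table 1 (printed in the Introduction) lists seven modified Rome IV criteria. Criterion 1 is "≤2 spontaneous bowel movements (SBMs) per week", and it defines an SBM as "a bowel movement that occurs in the absence of laxative, enema or suppository use in the preceding 24 hours". Entry requires "meeting ≥2 of the following criteria during the 2-week run-in period despite receiving treatment with PEG (min. 0.2 g/kg/day" daily), so at least two of the seven must be present while the child is on PEG.

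PEG is part of the design at each stage:
- Before entry, Table 1 requires that children "Are treated with PEG (minimum dose of 0.2 g/kg/day) for ≥1 month prior to inclusion in the study".
- During the run-in, Visit 1 in the Study schedule keeps the same minimum daily dose.
- During the intervention, Medication and co-interventions states: "Participants will continue their prestudy PEG dosage (≥0.2 g/kg/day"). It also permits other established laxatives.

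The Introduction names PEG as the preferred oral osmotic laxative. Nothing in Table 1 exempts maintenance PEG from the word laxative.

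Outcomes, Efficacy defines treatment success as resolution of functional constipation by Rome IV criteria at the end of the intervention, assessed by the investigator at screening and again at the end. In the same section, the list of diary endpoints describes the SBM differently: "Spontaneous bowel movements (>24 hours after escape medication").

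**The concern.** One term carries two incompatible definitions, and the one attached to the entry criteria does not work in children who take a laxative every day. Under Table 1, a movement within 24 hours of a PEG dose is not spontaneous. For a child who takes PEG daily, criterion 1 is therefore met whatever the stool frequency, and it stops separating children with infrequent stools from those without.

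Two decisions depend on it. At entry, a child with normal frequency and one other criterion qualifies. At the end of the intervention, the same child would still count as constipated, and a return to normal frequency could not contribute to treatment success. The McNemar analysis of that endpoint would carry the same error.

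Missed PEG doses distort the score in another way. They create SBMs, so a non-adherent child looks less constipated on criterion 1 than an adherent child with the same stool pattern.

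**Working it through.** **The plan's own figure.** The only computed figure is the sample size. With a two-sided alpha of 0.05, power 0.8, expected proportion 0.9, lower bound 0.7 and the variance taken at 0.9:

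n = (1.960 + 0.842)² × 0.9 × 0.1 / (0.9 − 0.7)² = 17.66, rounded up to 18.

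This reproduces the stated 18. No SBM definition enters it.

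**Step 1: SBMs per week under each definition.** Assumptions: one PEG dose every day and no escape medication.

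| Bowel movements/week | SBMs, Table 1 | Criterion 1 met? | SBMs, Efficacy section | Criterion 1 met? |
|---|---|---|---|---|
| 2 | 0 | yes | 2 | yes |
| 3 | 0 | yes | 3 | no |
| 7 | 0 | yes | 7 | no |
| 14 | 0 | yes | 14 | no |

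With a dose every 24 hours, every movement has a laxative dose in the preceding 24 hours. The Table 1 count is therefore 0 in every row.

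**Step 2: effect on the rule.** Let k be the number of criteria 2 to 7 that are present (0 to 6). With criterion 1 fixed as met:
- Entry requires 1 + k ≥ 2, that is k ≥ 1.
- Success at the end of the intervention, if the same list is used, requires 1 + k ≤ 1, that is k = 0.

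**Step 3: who changes class.** Seven yes/no criteria give 2⁷ = 128 profiles. The two definitions disagree only where criterion 1 is truly absent and k = 1. That is 6 profiles, one for each other criterion. With k = 0 both definitions say criteria not met. With k ≥ 2 both say met. With true infrequency both give the same answer.

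Example: a child has 7 movements a week, daily PEG and one other criterion.
- Table 1: 1 + 1 = 2 criteria, so eligible at entry and not a success at the end.
- Efficacy definition: 0 + 1 = 1 criterion, so ineligible at entry and a success at the end.

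**Step 4: dependence on adherence.** With one movement and one scheduled dose a day, each missed dose makes one movement an SBM. Criterion 1 stops being met at 3 SBMs a week, so at least 3 missed doses a week are needed. Below that, the result in Step 1 stands.

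**The case against.** The strongest reply is that the intended reading is clear. The Table 1 footnote scores the criteria despite PEG treatment, Medication and co-interventions separates PEG and stable co-laxatives from escape medication, and the Efficacy section refers to escape medication alone. On this view the Table 1 phrase is only loosely worded. The intention is probably as described, but the diary endpoint does not amend Table 1. Eligibility is confirmed from diaries against the modified criteria, so staff must use one definition or the other, and the two disagree.

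A reader might infer several stronger points that the documents do not support:
- **That every participant meets criterion 1 at both time points.** This needs full adherence. The Introduction describes adherence to PEG as usually poor, and dose reductions are allowed.
- **That Table 1's SBM wording is stated to apply at the end of the intervention.** It is not. The entry sections speak of modified Rome IV criteria and the Efficacy section of Rome IV criteria. Carry-over is a reasonable inference, because Table 1 is the only definition of functional constipation given.
- **That improved stool frequency would go unseen.** Defecation frequency and SBMs (by the escape-medication definition) are separate diary endpoints.
- **That success is understated by a known percentage.** The protocol gives no persistence rate for any criterion, so no percentage can be derived.
- **That items 4 and 7 should be merged.** Item 7, "History of large-diameter stools that may obstruct the toilet in toilet-trained children", overlaps item 4 on large-diameter stools. The list is taken from a cited diagnostic instrument, however, and changing its items could reduce comparability. This is a point for the sponsor to check.

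**Conclusion.** The point holds as an internal contradiction that gives wrong scores if Table 1 is followed as written. For a child taking PEG daily, criterion 1 is met at any stool frequency, and the two-criteria rule reduces to one other criterion. The error runs in one direction at each time point: over-inclusion at entry and, if the same criteria are used, under-counting of success at the end of the intervention.

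Its reach is limited. Only children without true infrequency who have exactly one other criterion change class (6 of 128 profiles), and the documents do not show how many children that would be. It affects eligibility and the secondary treatment-success endpoint with its McNemar test. The protocol itself says that no efficacy claims can be made without a control group. The primary feasibility criterion and the sample size of 18 do not depend on the definition.

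The conclusion rests on two assumptions: that PEG is taken daily or nearly so, and, for the success endpoint, that the Table 1 criteria are the ones applied at the end.

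**What to change.** Reconcile Table 1 with the Efficacy section by using one SBM definition in both. A bowel movement is disqualified only by escape medication in the preceding 24 hours; stable maintenance PEG and permitted stable co-laxatives do not disqualify it. State that this definition applies to criterion 1 at run-in and at the end of the intervention, and score criterion 1 from the existing diaries at both time points.

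Keep children who have already been treated in the feasibility denominator, because removing them afterwards would disturb the primary endpoint. Report how many met the entry criteria only under the current Table 1 wording.

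The cost is an amendment to two passages. No new data are needed, since bowel movements and escape medication use are already diary items. The downside is that some prospective children with a single criterion become ineligible. The documents give no count, but it is likely to be few in a study of 18. Separately, the sponsor should check whether items 4 and 7 are meant to count as two criteria.
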